## Discussion

This protocol describes the methodology for an RCT to examine the effectiveness of digital CBT for SUD—Breaking Free Online (BFO)—and fortnightly recovery check-in phone calls, when delivered as an adjunct to standard treatment, compared with standard treatment only, at an NHS Mental Health Trust in North-West England. This design could be interpreted as a limitation as it does not allow direct effectiveness comparisons to be made between digital treatment and in-person treatment. However, this design has been selected in order to enhance ecological validity of the study, as it most accurately reflects how BFO is delivered in treatment services, i.e., as an adjunct to standard treatments and not as a replacement.

Another limitation of the methodology is that it will not be possible for the investigators and practitioners to be blinded to the allocation of participants, which could potentially bias outcomes—however, the study statistician will be blinded to treatment allocation. Additionally, because the level of randomization will be at the level of individual service users, this may pose a risk of contamination across the two study groups if individual participants have an opportunity to interact with one another. Participants may also join the study at different points in their treatment and recovery journey—therefore a ‘floor effect’ could occur that may under-estimate the effectiveness of BFO if a proportion of participants start at a baseline of abstinence/low substance use and therefore relatively good psychosocial functioning.

Another potential limitation is the likely attrition rate from a study including individuals with SUD – previous research has demonstrated high levels of attrition in SUD intervention RCTs, especially when the intervention under investigation is digital [47, 48]. Individuals with SUD may have mental health difficulties, financial and accommodation instability, and may experience periods of lapse and relapse; each of these factors may create difficulties when trying to support such individuals to remain engaged with treatment programs [49, 50]. Although the fortnightly recovery check-in phone calls are intended to enhance retention of participants in the BFO arm of the study, it may be more challenging to retain participants in the study once the treatment period is over and they are no longer receiving the check-in phone calls—a prediction supported by previous systematic reviews into smoking cessation interventions [51]. Every attempt will be made to obtain follow-up data—as follow-up data is being collected via electronic methods, there is scope to send reminders to participants to complete follow-up assessments via email, a method indicated to be successful in increasing follow-up retention in previously conducted RCTs [52]. 

Despite the potential limitations of a study such as this, if BFO and the telehealth delivery approach included appear to support individuals to achieve recovery from SUD, findings could inform treatment delivery across SUD services more generally and could increase patient access to support even when in-person services may be restricted or unavailable.

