### Study setting

This study will be conducted at a single site within an NHS Mental Health Trust in North-West England. This Trust serves approximately 53,000 service users a year, and the clinical site where the study will be conducted usually receives approximately 2400 referrals of service users with SUD annually, with approximately 1500 of these referrals receiving structured treatment. The Trust provides a range of services for people with SUD including six rehabilitation units, community outreach and young person teams, and a citywide Recovery Pathways service.

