### Participants

Participants will be service users currently in treatment for SUD who meet the following inclusion criteria: (i) aged 18 years or above, (ii) experiencing problem alcohol and/or drug use for ≥ 12 months requiring treatment, as determined by clinical personnel at the service, (iii) willing to comply with an eight-week treatment program for problem alcohol and/or drug use, (iv) willing to provide outcome measures post-treatment, and at three and six-months follow-up, (v) able to read, write and communicate in the English language, (vi) willing and able to access an internet enabled device for the eight-week treatment period, (vii) willing and able to give informed consent for participation in the study, and capable of understanding and complying with protocol requirements.

Exclusion criteria are as follows: (i) under 18 years of age, (ii) participation in any other alcohol and/or drug related clinical studies within 12 months prior to date of consent, (iii) detention under the Mental Health Act, (iv) clinically significant intellectual or developmental disability which may impair ability to engage with BFO and/or complete the necessary assessment measures included in the methodology, (v) pregnancy (as self-reported), (vi) previous use of BFO to address drug or alcohol use within the past 12-months.

The projected sample size will require 61 evaluable participants in each of the two treatment groups (interventional and control) to achieve enough observed power (assuming an observed power of 0.80 with α = 0.05) with an allowance of 50% attrition at three and six-months follow-up, in order to detect a medium effect size (d ≤ 0.50). Therefore, to obtain a total of 122 evaluable participants, it is estimated that a total of 183 participants will need to be recruited and screened. These estimations have been based on previous alcohol and drug studies size samples [8], some of which have used longitudinal statistical analyses.

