### Outcomes

Outcomes data will be collected via self-report, with participants completing an online assessment containing a series of standardized psychometric measures at Baseline, End of Treatment, and 3-month and 6-month follow up timepoints. Additionally, engagement data (time spent accessing the program, number of BCTs engaged with) will be collected automatically via the BFO backend database for those participants in the interventional arm.

The primary outcome will be self-reported substance use compared to baseline following treatment completion, and at three and six-months follow-up, which will be measured using the following questions:Weekly use of primary problem substance (i.e., ‘How many days in the past week did you use [primary substance]?’‘How much [primary substance] did you use each day?’)

Secondary outcomes will be measured at corresponding time points using the following standardized measures:Severity of Dependence Scale (SDS) [37, 38]: A five-item scale measuring severity of substance dependence—internal reliability: α = 0.81–0.90; test–retest reliability ICC = 0.89.Patient Health Questionnaire-4 (PHQ-4) [39]: A four-item scale that measures severity of depression and anxiety—internal reliability, α = 0.81.Five items (1, 2, 17, 18, 20) from the World Health Organization Quality of Life scale (WHOQoL-BREF) [40]—internal reliability of these five items, α = 0.84.Recovery Progression Measure (RPM) [34, 35]: A 36-item scale measuring functioning in six biopsychosocial domains functioning that are implicated in all SUDs and recovery from SUDs—internal consistency, α = 0.89; test–retest reliability, ICC = 0.73.

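### People with no current use can enter a trial whose primary outcome is past-week use; the protocol concedes the effect may be under-estimated but states no mitigation.

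*Protocol article*

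**What the plan says.** Protocol article, Participants: "Participants will be service users currently in treatment for SUD who meet the following inclusion criteria". The substance-use criterion is "experiencing problem alcohol and/or drug use for ≥ 12 months requiring treatment, as determined by clinical personnel at the service". None of the seven inclusion criteria sets a minimum of recent use. None of the six exclusions, which end with "previous use of BFO to address drug or alcohol use within the past 12-months", removes people who are currently abstinent.

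Outcomes: "The primary outcome will be self-reported substance use compared to baseline following treatment completion, and at three and six-months follow-up". It is measured by the number of days of use in the past week and the amount used per day.

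Discussion: participants may join at different stages of recovery, and a floor effect "could occur that may under-estimate the effectiveness of BFO if a proportion of participants start at a baseline of abstinence/low substance use". The blinding limitation in the same paragraph is followed by a countermeasure, the blinded statistician. The floor effect is followed by none.

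Randomization describes an individual random sequence in sealed envelopes and mentions no strata. Data analysis and management plans ANCOVA, mixed models, and regression on baseline dependence, mental health, psychosocial functioning and quality of life. Its sub-groups are introduced by examples: age, gender, primary substance, depression and anxiety. Baseline substance use is named in neither list.

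**The concern.** Someone who reports zero days of use at baseline cannot reduce that number. They can only stay at zero or relapse. If such people form a sizeable part of the sample, two things follow.

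First, the average effect is diluted, while the sample size rests on d = 0.50 with no stated allowance for this. Second, the single average answers two different questions at once: whether BFO reduces use in people who are using, and whether it prevents relapse in people who are not. A null result could then mean that BFO does not work, or that too little use was left to reduce, and the main analysis could not tell these apart.

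**Working it through.** **The plan's own figure.** The inputs in Participants are d = 0.50, α = 0.05 (two-sided assumed) and power 0.80. The normal approximation gives n = 2(1.96 + 0.84)²/0.50² ≈ 63 per arm, and the t-test gives 64. The stated 61 is close; its t-test power at d = 0.50 is 78%.

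**Assumptions for the illustration.** None of these is in the documents.
- f is the share abstinent at baseline, taken from 0 to 40%.
- Baseline users: control mean at follow-up 4 days, SD 2.5, BFO effect 1.25 days. So d = 1.25/2.5 = 0.50.
- Baseline abstainers: mean at follow-up 0.7 days, SD 1.7, BFO effect e. First e = 0, then e = 0.25 and 0.35 days.
- The days question only, 61 evaluable per arm, two-sided t-test at 0.05.

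**Formulas.**
- Average effect: Δ = (1 − f) × 1.25 + f × e
- Variance within the two groups: W = (1 − f) × 2.5² + f × 1.7²
- Variance between the two groups: B = f(1 − f) × (4 − 0.7)²
- Unadjusted test: d = Δ/√(W + B)
- Adjusted for baseline abstinence, ideal case: d = Δ/√W
- Baseline users only: d = 0.50 with 61(1 − f) per arm

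**Worked case, f = 30%, e = 0.** Δ = 0.7 × 1.25 = 0.875. W = 0.7 × 6.25 + 0.3 × 2.89 = 5.242. B = 0.21 × 10.89 = 2.287. Unadjusted d = 0.875/√7.529 = 0.32, power 42%. Adjusted d = 0.875/√5.242 = 0.38, power 55%. Users only: 42.7 per arm, power 63%.

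**Power, with e = 0.**

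| Abstainers | Unadjusted d | Unadjusted | Adjusted | Users only |
|---|---|---|---|---|
| 0% | 0.50 | 78% | 78% | 78% |
| 10% | 0.43 | 65% | 72% | 74% |
| 20% | 0.37 | 53% | 64% | 69% |
| 30% | 0.32 | 42% | 55% | 63% |
| 40% | 0.27 | 32% | 46% | 56% |

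**If abstainers also benefit.** With e = 0.25 days, the adjusted all-randomised test has power of 74/68/62/56% at 10/20/30/40% abstainers, practically equal to users only. With e = 0.35 days, half of the assumed 0.7, it has 74/70/65/60%, equal or better.

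**Cross-check.** With the SD held fixed and d simply scaled to 0.50 × (1 − f), the normal approximation gives power of 70/60/49% at 10/20/30%. The loss does not depend on the mixture variance alone.

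**The case against.** A reader might infer that nothing in the analysis deals with baseline status. The document does not support that. The primary outcome is compared with baseline, ANCOVA, regression and mixed models are planned, and the sub-group list is open. Adjustment for baseline use would remove the between-group variance B, so the unadjusted column is the worst case. Strata, covariates and further sub-groups may also be set out in the full protocol or an analysis plan, neither of which is available, so their absence from a condensed article is weak evidence. The firm parts are the entry list, which is printed in full, and the limitation that is admitted without a countermeasure.

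A reader might also infer bias between arms. Randomisation rules that out for the enrolled mix. Nor is it true that abstainers cannot benefit. They cannot fall below zero, but the Introduction describes BFO as informed by relapse prevention, follow-up runs to six months, and a lower relapse rate than control would be a real effect.

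The d = 0.50 is stated for the trial's participants. If the earlier studies behind it already included people in recovery, the calculation dilutes it twice. The criterion also speaks of people experiencing problem use that needs treatment, which clinicians might read as current use; the Discussion, however, itself allows for abstinent or low-use entrants.

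These points limit the size of the problem and the choice of remedy. They do not remove it: the regression is aimed at imbalance between arms, baseline use is not named in it, a Kruskal-Wallis test takes no covariates, and adjustment restores precision without restoring the diluted effect.

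**Conclusion.** The point holds as a matter of power and interpretability. The entry criteria and the primary outcome do not fit each other well, the protocol says so, and the plan as written yields one blended average.

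The size is unknown because the abstainer share is not given. Under the assumptions shown, 20% abstainers would take power from 78% to 53% unadjusted or 64% adjusted, and 30% would take it to 42% or 55%. These figures depend on the assumed means and SDs, on d = 0.50 applying to current users, and on no benefit in abstainers.

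A stronger conclusion is tempting: that the main test should move to baseline users, or that a recent-use criterion must be added. The figures do not support either as a required correction. The advantage of testing users only vanishes once abstainers gain about 0.25 days, moving the main test would depart from the stated intention-to-treat analysis of all randomised participants, and changing entry during recruitment would mix two populations.

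**What to change.** 1. Keep all randomised participants as the main analysis and name baseline use of the primary substance as a covariate in it.
2. Before unblinding, and before any interim comparison by arm, pre-specify two further analyses beside the main one: the primary outcome in randomised participants with at least one day of past-week use at baseline, as a key supporting analysis; and relapse (any use) in those with none.
3. For the remaining allocations, use separate envelope series for none versus any past-week use at baseline. The answer must be recorded before the envelope is opened. The same order is needed for the two sub-sets to keep the protection of randomisation.

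The cost is a few lines of analysis text and some envelope administration; the data are already collected. The sub-sets are smaller: at 30% abstainers, about 43 users and 18 abstainers per arm among 61. The relapse analysis would therefore be mainly descriptive.

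A recent-use entry criterion is an option for the investigators to weigh against generalisability. The site has "approximately 1500 of these referrals receiving structured treatment" a year against a recruitment target of 183, which suggests room for one. A window longer than a week would still admit zeros on a past-week outcome.

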## Data Availability

Not applicable.

## Abbreviations

AE: Adverse event
ANCOVA: Analysis of covariance
ANOVA: Analysis of variance
BCT: Behavioral change technique
BFO: Breaking free online
CAT: Computer-assisted therapy
GMMH: Greater Manchester mental health
ITT: Intention to treat
LBM: Lifestyle balance model
NHS: National Health Service
PHQ-4: Patient health questionnaire-4
RCT: Randomized controlled trial
RPM: Recovery progression measure
SDS: Severity of dependence scale
SPSS: Statistical package for the social sciences
SUD: Substance use disorders
ITT: Intention to treat
WHOQoL-BREF: World Health Organization Quality of Life Scale
